**Treatment target hierarchy for over-control**	
1. Life-threatening behaviours	**Suicidal ideation and non-suicidal self-injury** *Over-controlled self-injurious behaviour tends to be planned in advance, occurs in private and rarely requires immediate medical attention*
2. Therapeutic alliance ruptures	**Patient feels misunderstood or perceives therapy as not relevant to their problems** *Signals of non-engagement by over-controlled patients tend to be understated, for example saying “hmm”, “maybe” or “I guess so” when disagreeing, or by avoiding eye contact or changing the topic when feeling misunderstood*
3. Over-controlled Behavioural themes	**Constrained expressions of emotion** *Over-controlled patients tend to display inhibited, flattened or insincere facial expressions (eg, smiling when distressed, showing concern when not feeling it), have a monotonic voice tone and tight and non-expansive gestures or body movements. They will work hard to avoid public displays of emotion* **Overly cautious and hyper-vigilant** *Over-controlled patients are not necessarily avoidant but guarded, wary and suspicious. They exhibit superior detailed-focused processing* **Rigid and rule-governed behaviours** *The actions of over-controlled patients tend to be non-mood dependent and instead follow certain self-imposed rules. They are motivated by social obligation and exhibit high moral certitude; they often make self-sacrifices to care for others or to do the ‘right’ thing. They tend to be hyper-perfectionistic and have compulsive needs for order and structure* **Aloof and distant relationships** *Over-controlled patients do not necessarily lack contact but lack social connectedness with others. They are slow to warm-up and will walk away or abandon a relationship when in conflict. They are likely to feel like an outsider, different or detached from others* **Envy, Resentment, Bitterness and Revenge** *Over-controlled patients tend to be performance-focused, engage in social comparisons, are secretly competitive, tend to hold grudges and may have secret pride in superior capacities for self-control. They may take pleasure in a rival failing or feel unappreciated for personal self-sacrifices or efforts on their part to meet or exceed expectations*

Targets higher in the treatment hierarchy take priority over lower ones. Thus, life-threatening behaviors and therapeutic alliance-ruptures take precedence over behavioral themes when these are present. Therapists use the behavioral themes to facilitate treatment planning.

#### Therapist training and supervision

All therapists had to complete a two-part, 10-day RO-DBT intensive training course over 6 months and additional training or supervision when needed to achieve adherence to the treatment manual. We videotape all treatment sessions and shall sample 10% of both therapy sessions and skills classes at random, stratified by therapist and participant, for adherence rating.

### Discontinuations

If participants are unable or unwilling to attend RO-DBT sessions, we consider them as treatment drop-outs but encourage them to provide outcome data. If they withdraw from data collection, we permit them to continue with RO-DBT. If they withdraw consent to participate in the study, however, we do not seek further data.

### Outcome measures

Table 1 summarises the schedule of outcome measures.

### Primary outcome

The primary outcome is depressive symptoms, measured on the 17-item Hamilton Rating Scale for Depression (HAM-D)^36^ at four points (baseline, and 7, 12 and 18 months after randomisation) by assessors who report their ‘blindness’ after each assessment. We replace them with unblinded assessors for subsequent assessments.

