**Methods and analysis:**

REFRAMED is a multicentre randomised controlled trial, comparing 7 months of individual and group RO-DBT treatment with treatment as usual (TAU). Our primary outcome measure is depressive symptoms 12 months after randomisation. We shall estimate the cost-effectiveness of RO-DBT by cost per quality-adjusted life year. Causal analyses will explore the mechanisms by which RO-DBT is effective.

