## Methods

### Design and setting

REFRAMED is a multicentre, randomised controlled trial conducted at three National Health Service (NHS) sites in the UK—Dorset, Hampshire and North Wales. These sites routinely offer outpatient psychological treatment. All trial participants receive TAU, but those allocated at random to the experimental arm also receive 7 months of RO-DBT. We also allocate participants at random between non-therapeutic alternatives designed to facilitate mediational analyses. We measure clinical outcomes at four time points—baseline, and 7, 12 and 18 months after randomisation, using assessors blind to participants’ allocated treatment.

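### The rule for replacing HAM-D assessors is worded backwards: it brings in unblinded raters, contradicts the blinded-assessor design, and does not say when replacement happens

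*Protocol article*

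**What the plan says.** Three places in the protocol article bear on who rates the primary outcome.

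- **Design and setting.** Clinical outcomes are measured at "baseline, and 7, 12 and 18 months after randomisation", "using assessors blind to participants’ allocated treatment". No exception is made for any time point.
- **Primary outcome.** The 17-item HAM-D is rated at the same four points "by assessors who report their ‘blindness’ after each assessment". The next sentence is the whole of the replacement rule: "We replace them with unblinded assessors for subsequent assessments".
- **Abstract, Methods and analysis.** The primary time point is fixed: "Our primary outcome measure is depressive symptoms 12 months after randomisation".

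**The concern.** The design section promises blind raters throughout. The operating rule for the primary outcome, read as written, replaces assessors with people who know the allocation.

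This matters because the HAM-D is scored by an assessor at interview and involves judgement. The Design implications and limitations section says there is no active comparator, so a rater who knows the arm also knows who received the new therapy. Blind rating is an important stated safeguard against assessor bias in this outcome. The same scores also feed the remission outcome (Secondary outcomes) and the HAM-D cost-effectiveness sensitivity analysis (Economic evaluation), so an ambiguity about the rater carries over to those results.

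Loss of blinding is also a realistic event in this trial. Table 1 places the service-use schedule at the same follow-up visits as the HAM-D, and participants may mention their therapy when asked about services. The plan therefore needs a replacement rule that works, and the one it prints does not.

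**Working it through.** The point rests on wording, so there is no figure to reproduce. The check sets the statements side by side.

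**Step 1: direction.**

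| Section | Who rates later HAM-D assessments |
|---|---|
| Design and setting | Assessors blind to allocation, all four time points |
| Primary outcome, replacement sentence | Unblinded assessors |

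The two are opposites. The replacement sentence is complete and grammatical, it is current text, and there is no sign of a gap or broken table around it.

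**Step 2: trigger.** The pronoun *them* refers back to the assessors of the preceding sentence, which means all HAM-D assessors. Nothing limits it to an assessor who has reported losing blinding, or to the participant concerned. Deleting the prefix *un* would correct the direction but would still leave every assessor being replaced, with no stated condition. The sentence therefore has two defects.

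**Step 3: reach under the literal reading.** There are four HAM-D occasions: baseline and 7, 12 and 18 months. The Randomisation section places allocation after the baseline questionnaires are received, so there is no allocation to know at baseline. Two start points are possible:

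- Replacement starts after baseline: 4 − 1 = 3 occasions are affected (7, 12 and 18 months), that is, every post-randomisation rating.
- Replacement starts after the 7-month rating: 4 − 2 = 2 occasions are affected (12 and 18 months).

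The 12-month primary outcome falls under the rule in both cases.

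**Step 4: is the conflict resolved elsewhere?** The Eligibility section monitors inter-assessor reliability with kappa, which measures agreement between raters and not knowledge of allocation. The Data collection and management section refers to trained assessors and standard operating procedures but does not mention blinding. No other section qualifies the sentence.

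**Step 5: which statement was intended?** Asking assessors to report on their blinding has a purpose if those who become unblinded are then replaced by blind ones. It has little purpose if unblinded raters are to be brought in anyway. Taken with the plain statement in Design and setting, this makes a slip in the replacement sentence much the more probable explanation.

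**The case against.** The strongest reply is that this is an obvious slip. The design section is clear, the blinding report would be pointless under the literal reading, and a sensible reader will supply the intended meaning. That largely stands. It makes this an inconsistency in the text and not a flawed design choice. It does not remove the need to correct the text: the sentence is the only operating rule printed for the primary outcome, and repairing it takes more than deleting a prefix, because the trigger is missing too.

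Stronger readings are tempting, and the document does not support them:

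- *That the 12-month HAM-D was, or will be, rated unblinded.* The article shows a badly worded rule, not conduct. Nothing in it reports an assessment made by a deliberately unblinded rater.
- *That a bias of some number of HAM-D points follows.* The article gives neither a rater shift nor a share of unblinded ratings. A shift common to both arms would cancel in the comparison; only a difference between arms would bias it.
- *That blind rating is the trial's sole defence.* Blinding status is recorded after each rating, so its loss can be seen, and the self-reported PHQ-9 is collected monthly to month 12 and at month 18 (Table 1). Neither replaces blind rating of the primary outcome, but both exist.
- *That a sensitivity analysis limited to ratings reported as blind must be added.* Such an analysis is ordinarily left to the SAP, which is not shown. It would also select on an event after randomisation that may be commoner in the RO-DBT arm, so it could introduce bias of its own.

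A last objection is timing. The Current progress section reports recruitment from March 2012 to May 2015, so many 12-month ratings were probably complete when the article was written, and a correction cannot alter them. That is right. But data collection was planned to run to June 2016, and participants recruited in May 2015 reach 12 months in May 2016, so a correct rule could still guide some ratings. For the rest it clarifies the record.

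**Conclusion.** The concern holds as an internal inconsistency, probably a drafting error. The replacement rule in the Primary outcome section is reversed relative to Design and setting and has no trigger. If it were followed literally, unblinded raters would score the 12-month primary outcome and at least one further follow-up. The document does not show that this happened.

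The size is qualitative. A reader cannot establish from the operating rule who rates the primary outcome, and someone assessing risk of bias would have grounds to mark the trial down on the printed wording. The contradiction itself rests on no assumption. The view that it is a slip rests on the purpose of the blinding report and on the clear statement in the design section.

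**What to change.** Reconcile the Primary outcome section with Design and setting by replacing the sentence. For example:

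> An assessor who reports becoming unblinded to a participant's allocation is replaced by an assessor still blind to that allocation for that participant's subsequent assessments.

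This corrects the direction, states the trigger, and ties replacement to the individual participant. Before publishing the correction, the sponsor should check it against the standard operating procedures that assessors actually follow, so that the printed rule describes real practice.

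The cost is one sentence and that check. Blinding status is already recorded after each assessment, so no new data collection is needed, and sample size and the primary analysis are unaffected.

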### Secondary outcomes

Secondary outcomes at the same four points include remission status, and suicidal ideation and behaviour. We define remission as the combination of a HAM-D score of less than 8 and minimal functional impairment on the Longitudinal Interval Follow-up Evaluation—Range of Impaired Functioning Tool (LIFE-RIFT);^50^ we measure suicidal thoughts and behaviours on the Modified Scale for Suicidal Ideation^52^ and the Suicidal Behaviors Questionnaire.^57^

### Health economics data

We collect health economic data alongside our primary outcomes. For health costs we use the Adult Service Use Schedule (AD-SUS); and for health utility the European Quality of Life Questionnaire (EQ-5D-3 L).^46^ The AD-SUS measures medication and service use, and lost productivity due to illness, in mental health populations, including patients with depression.^39^ We also ask therapists about unscheduled time in treating RO-DBT patients, notably calls out of hours.

### Mediators of outcome

We collect data on potential outcome mediators throughout the treatment and follow-up using questionnaires to measure interpersonal, emotional, and psychosocial functioning, strength of therapeutic alliance, use of skills taught in treatment and expectancy (table 1).

Between these questionnaires, we collect data on mood, emotional coping and the credibility of and expectancy attached to the intervention, once a month for the first 12 months and again at 18 months. We also use an automated telephone system to measure mood (PANAS Short-Form),^72^ coping skills (6 items from the DBT-WCCL)^44^ and self-compassion (Self-Compassion Scale)^59^ once a week over the first 6 months that participants are in the trial.

### Moderating variables

At baseline we collect data on potential moderating variables, including basic demographics and Axis I and Axis II disorders, childhood experiences and invalidation, and personality and markers of personality disorder (table 1). To control for social desirability, we ask participants to complete the Balanced Inventory of Desirable Responding-Short Form. (Hart CM, Ritchie T, Hepper EG, *et al*. The Balanced Inventory of Desirable Responding Short Form: Reliability, validity, and factor structure. submitted manuscript 2012).

### Characteristics of therapists

To investigate whether therapist characteristics, and their relationship with patient characteristics influence outcome, we collect measures of perfectionism (Frost Multidimensional Perfectionism Scale),^47^ personal values (Schwartz Values Scale)^61^ and attachment experiences (Measure of Parenting Style).^51^ To provide an instrumental variable for strength of therapeutic alliance, we measured therapists’ capacity to generate strong alliances before the trial by asking several patients from the caseload of each therapist to complete the California Therapeutic Alliance Scale.^41^

### Sample size estimation

Based on an average effect sizes close to one from two RO-DBT pilot trials for RD^32^
^33^ and one pilot trial of DBT for TRD,^73^ we judged it feasible and desirable to power REFRAMED to detect a standardised difference of 0.4 between-groups (RO-DBT and TAU)—likely to be considered clinically relevant by the UK National Institute of Health and Care Excellence (NICE).

In the absence of intraclass correlation, a sample of 200 analysable participants from the three centres would yield 80% power when using a significance level of 5% to detect a mean difference of two points on the HAM-D, equivalent to a standardised difference of 0.4. Since we expect to collect analysable data from 83% of participants, we increased our initial target to 240. To increase the power of our mechanistic analyses, we planned to randomise 144 of these to RO-DBT. As participants receiving RO-DBT are clustered by therapist, we increased the target RO-DBT sample size from 144 to 180 to allow for an intracluster correlation coefficient of 0.025 for HAM-D scores, and an average cluster size of 11. Thus we aim to randomise 276 patients—180 to RO-DBT and 96 to TAU (a final allocation ratio of 15:8).

### Statistical analyses

For our primary measure of depression (HAM-D), we shall analyse by treatment allocated and use a mixed-effects model to estimate the effectiveness of RO-DBT. This will include random effects to account for clustering of outcomes by therapist, and fixed effects to account for treatment allocation, differences between sites and their interaction. In particular, this model does not assume that all therapists are equally effective.^74^ Covariates will include baseline HAM-D score, diagnosis of PD at baseline and age at first onset of depression. Repeated HAM-D measurements enable us to compare RO-DBT and TAU at 7, 12 and 18 months after randomisation. Secondary analyses will test for interaction between treatment allocation and covariates, and estimate the marginal effect of RO-DBT within strata. If data are missing at random (MAR), these models will be unbiased and efficient. We shall, therefore, analyse missing data thoroughly and qualify our conclusions accordingly.

### Mechanisms, instrumental variables and causal analyses

Initially our causal analysis will consider each potential mediator in turn, estimating both the direct effect of treatment via exposure, and the indirect effect via the mediator. Following Baron and Kenny,^75^ we shall compare the resulting estimates with those from a naïve analysis that assumes no unobserved confounding, and state the assumptions under which the causal estimates are unbiased and consistent. Finally we shall extend these analyses to a joint model of all mediators and IVs. To explore patterns of temporal ordering from skill acquisition, through development of the therapeutic alliance, to changes in depressive symptoms, we shall use multivariate growth curve models including autoregressive and lagged terms.

### Economic evaluation

We shall undertake cost-utility analysis to estimate the cost effectiveness of RO-DBT relative to TAU alone in terms of cost per Quality-Adjusted Life Year (QALY) derived from the EQ-5D-3L. We shall use cost-effectiveness analysis of depressive symptoms from the HAM-D as sensitivity analysis. Our primary perspective will be that of the NHS and personal social services, as preferred by the National Institute for Health and Care Excellence (NICE).^76^ Again we shall consider societal losses due to lost productivity, including both absence from work and reduced productivity during work, in the sensitivity analysis. We shall estimate cost-effectiveness through both approaches used to estimate clinical effectiveness: conventional analysis by treatment allocated, and IV analysis based on treatment received, that is adherence. We shall use non-parametric bootstrapping to generate the joint distribution of mean incremental costs and effects of RO-DBT relative to TAU and thus, explore the probability that one treatment is better, given NICE's ‘willingness-to-pay’ threshold of £20 000 to £30 000 per QALY. We shall summarise uncertainty around these estimates by cost-effectiveness acceptability curves.^77^

### Data collection and management

#### Paper data

To ensure accuracy, completeness and reliability, trained assessors collect outcome data during interviews in person or by phone by following standard operating procedures for data collection and transfer to the trial office in Southampton. Each month we post additional paper questionnaires direct to participants with a free return envelope, and send text or email reminders after 10 days.

#### Electronic data capture system

We enter all paper data twice onto Signalbox (http://www.thesignalbox.net), a validated electronic data capture system. This system also collects the data from automated phone calls and therapists’ treatment notes online, notably by issuing weekly electronic reminders.

#### Study monitoring

The Trial Steering Committee (TSC) and Data Monitoring Committee (DMC) monitor the trial to ensure we comply with the rigorous standards defined in the Medical Research Council's (MRC) Guidelines for Good Clinical Practice. The TSC meets twice a year throughout the trial. The DMC met twice in the first year and annually since then. Both the TSC and DMEC are independent from the Funder and Sponsor.

### Reporting of adverse events and study termination

Site principal investigators (PIs) monitor and assess serious adverse events (SAEs) and report them to the chief investigator immediately, and to the DMC regularly, or immediately when the SAE is a Suspected Unexpected Serious Adverse Reaction (SUSAR). Site PIs discuss SAEs with the relevant participants and their GPs with their permission. The trial will terminate if the TSC, on the recommendation of the DMC or the chief investigator, judges it necessary for the welfare of trial participants or for the scientific validity of the trial.

### Ethical considerations and dissemination

We ask trial participants to give consent on three occasions:
Oral consent to the phone screen;Signed consent for the baseline assessment, stating that they have read and understood the information sheet and giving permission for the interview to be audio recorded;Eligible participants sign the reverse of their consent forms, stating that they understand the patient information sheet and are willing to participate in the trial.

Personal information will kept on secure databases (one for each site), only accessible to members of staff who need these details for making assessment appointments and sending letters. These are the only files that link personal information with the participant identification numbers.

We conduct REFRAMED in accordance with the Declaration of Helsinki. We have received approval from the Hampshire Research Ethics Committee (National Research Ethics Service (NRES) reference number 11/SC/0146) and the Ethics & Research Governance Department of the University of Southampton, the Sponsor. REFRAMED has insurance cover under the Sponsor's Professional Indemnity and Clinical Trials policy. All investigators comply with REFRAMED's policy on conflicts of interest, and will report conflicts of interest in all resulting publications.

We shall implement and report REFRAMED in accordance with all relevant CONSORT guidance. We plan to publish the findings in high-impact, peer-reviewed journals and disseminate them to service providers and users across the UK and beyond via public forums and websites. In accordance with Research Council guidelines, we shall store anonymised individual patient data from REFRAMED in a repository accessible by other researchers following publication.

## Discussion

REFRAMED is a randomised controlled trial of a promising treatment for refractory depression with implications for other diagnoses. It will contribute to the clinical literature in three ways:
Our broad selection criteria include patients routinely excluded from depression trials, namely those with comorbid personality disorder, suicidal behaviour, non-suicidal self-injury, prior psychotherapy, frequent relapse or older age. Hence the evidence base is weak for these patients in most need of effective treatment. Our inclusion criteria may mean that this trial will have a higher rate of reported suicide attempts than trials that exclude patients with PDs, comorbid disorders and suicidal ideation. However, our use of open criteria reflects the growing recognition that symptoms of many mental health conditions may share a common aetiology, and that to exclude patients with comorbidities significantly undermines the generalisability and utility of clinical trials.RO-DBT offers a major change in approach to the treatment of refractory depression. Most important is a novel focus on behavioural over-control as a core aetiological factor. The treatment proposes a new mechanism of therapeutic change by linking *neuoregulatory theory* and the *communicative functions of emotional expression* to the *formation of close social bonds.* This translates into novel skills focused on social signalling and changing psychophysiological arousal—a key component differentiating RO-DBT from other treatments.REFRAMED is the first mental health trial to use instrumental variables to analyse causes of mediation. In particular, we have randomised RO-DBT participants between eight combinations of three contextual features that are not intended to be therapeutic in their own right, but may affect mediating variables, including strength of therapeutic alliance and adherence to the treatment. This approach will yield estimates of the effects of mediating variables that are less biased by confounding than conventional estimates. Thus it has the potential to resolve a longstanding criticism of the literature that links strength of therapeutic alliance with outcome—that patients most likely to recover are those most able to form strong alliances.

